### Participant timeline {13}

Schedule of the study procedures is shown in Table 1.

**Table 1 Tab1:**
[figure not shown]
Schedule of study procedures

### Sample size {14}

The sample size calculation was conducted using the PASS software version 25 (NCSS, LLC. Kaysville, Utah, USA). Previous studies have shown that one-year recurrence rate of stroke patients in China was 17.7% [1]. The underlying assumption was a decline of the recurrence rate of stroke from 17.7% to 14.7%. The sample size of the experimental group and the control group was about 3168 with at least 90% power and an overall two-sided alpha level of 0.05. Taking approximate dropouts of 15% into account, the number of participants recruited was estimated to be 3727 each group. Therefore, 8000 patients will be recruited for this trial.

### Recruitment {15}

We will recruit 8000 subjects from the following 78 hospitals.The list of recruitment hospitals can be found in supplementary material 1.

## Assignment of interventions: allocation

### Sequence generation {16a}

This study is a real-world trial, with subjects assigned to this trial based on their actual conditions and wishes.

### Concealment mechanism {16b}

This study is an open-label, real world trial. So the patients and doctors know the exact grouping. We will further upgrade WeChat Mini Programs to automatically remind patients of medication and send forms for patients to fill in their medication. The research assistant is mainly responsible for collecting information about the patient’s condition, and do not know their medication. At the end of the whole research cycle, biostatisticians will unblind and analyze the data.

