### Relevant concomitant care permitted or prohibited during the trial {11d}

Medications applied to treat the underlying diseases (such as diabetes, hyperlipidemia and hypertension and others) are permitted. However, any medications used in this study should be documented in detail in case report form (CRF), including name, dose, dosage regimen, indication, and treatment period.

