### Implementation {16c}

Doctors will recruit patients with ischemic stroke who meet the inclusion criteria, and give them standardized treatment. Research assistants invite the patients into the patient management Wechat group and collect the baseline information of the patients. Biostatisticians are responsible for collecting and analyzing the uploaded data of each center. It embodies the characteristics of real world research in the process of implementation.

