#### Unblinding and allocation

At the end of the study cycle, the researchers will reveal the actual medication information of the patients, taking patients with good butylphthalide compliance as the butylphthalide group, and patients without taking butylphthalide and patients with poor compliance as the control group, and compare the difference of outcomes between the two groups.

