## Assignment of interventions: blinding

### Who will be blinded {17a}

A research assistant will be responsible for following up the participants in every research center. Researchers, research assistants and statisticians will be masked to allocate treatment throughout the treatment period. No blindness is allowed only in the event of serious adverse events (SAE) or emergency rescue. Statistical analysis will be conducted by independent statisticians who only know the group code and do not know the corresponding interventions.

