### Data management {19}

All data will be documented on CRF that records all information at baseline and follow-up, and immediately uploaded in the database through the EDC (Electronic Data Capture) system. The CRF includes demographic data, living habits, medical history, follow-up data, and adverse events. The data will be entered into the database by a designated operator and checked repeatedly by the research center. The whole process is anonymous. In order to protect the privacy of patients, their registration number will be used instead of their real name when filling out the form. Dropouts and adverse events (adverse events) will be recorded in a timely manner. In order to ensure the high quality of the trial, members of the Quality Management Committee will train all researchers involved in the trial in accordance with standard operating procedures before the trial starts.

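### The article promises a code-only masked analysis, yet has the biostatisticians unblind before analysing, and nothing stated keeps group formation and matching apart from the outcomes

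*Protocol article*

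**What the plan says.** Four places in the protocol article bear on who knows the groups and when.

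- **Who will be blinded {17a}**: "Researchers, research assistants and statisticians will be masked to allocate treatment throughout the treatment period". The section ends with a statement about the analysis itself: "Statistical analysis will be conducted by independent statisticians who only know the group code and do not know the corresponding interventions".
- **Concealment mechanism {16b}**: after describing the trial as open-label, with patients and doctors aware of the grouping, it says: "At the end of the whole research cycle, biostatisticians will unblind and analyze the data".
- **Unblinding and allocation** (under Real world research settings): "At the end of the study cycle, the researchers will reveal the actual medication information of the patients". The same sentence then forms the groups (good compliers with butylphthalide against non-takers plus poor compliers) and compares their outcomes.
- **Implementation {16c}**: "Biostatisticians are responsible for collecting and analyzing the uploaded data of each center".

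The grouping rule is in Explanation for the choice of comparators {6b} and in the legend of Fig. 1. Compliance is tablets taken divided by tablets due, and 80% to 120% counts as good. Statistical methods {20a} names propensity score matching as the means of balancing covariates.

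**The concern.** In a randomised trial the group code is fixed before any outcome occurs, so opening it late changes nobody's group. Here patients choose their treatment, and the analysed group is a derived variable. It is built at the end of the study from recorded intake, and poor compliers are placed in the control group. If the people who derive it, or who then build the matched set, can also see who had a recurrent stroke, decisions on doubtful intake records, early stoppers and the matching can drift towards the expected answer without anyone intending it. A coded analysis would guard against this, and the article claims one. The question is whether the procedures it describes deliver that.

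**Working it through.** The plan gives no figure on this point, so the check is mainly textual.

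**Step 1. Do the two statements on the analysts conflict?** {16b} has the biostatisticians unblind and then analyse. {17a} has the analysing statisticians know only a code. One might try to reconcile them through the limit in {17a} to the treatment period, which would allow unblinding afterwards. That limit belongs to the sentence on masking in general. The last sentence of {17a} is about the statistical analysis, which comes after treatment, and has no such limit. The conflict stands. There is a second one: in {16b} the biostatisticians unblind, whereas in Unblinding and allocation the researchers do.

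**Step 2. Could the analysts identify the groups from the data they hold?** {16c} does not mention medication or group formation. The link is indirect. Relevant concomitant care {11d} puts all medications in the CRF, and Data collection adds CRF forms on medication that patients complete. Data management {19} then says "All data will be documented on CRF that records all information at baseline and follow-up, and immediately uploaded in the database". {16c} gives the biostatisticians the uploaded data of each centre. A coded extract would be compatible with this, but none is described.

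**Step 3. When are the groups and the matched set formed?**

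- Outcomes are collected at months 1, 3, 6 and 12 after discharge (Study setting {9}; Outcomes {12}) and uploaded as they arise ({19}).
- Groups are formed at the end of the study cycle ({6b}; Unblinding and allocation).
- A propensity score is the probability of being in the butylphthalide group given baseline covariates. It cannot be fitted until each patient has a group.

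So grouping and matching both come after the recurrences are in the database. No section says that those who carry out these steps are kept from the outcome fields.

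**Step 4. How much judgement is left in the grouping?** The 80% to 120% rule is numeric and set in advance. Some latitude remains on duration: {6b} speaks of taking the drug for 3 months, Unblinding and allocation of good compliance, and Intervention description {11a} of 90 consecutive days or more. The number of tablets due, which is the denominator of the rule, is therefore not fully fixed for patients who stop early or continue longer. Intake is patient-reported, by daily diary or form.

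**Step 5. Illustrative worst case.** Assume 8000 patients split 4000/4000, with the plan's 17.7% recurrence in both groups: 0.177 × 4000 = 708 events each. Move m patients with recurrence from butylphthalide to control, and nobody else.

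- The rates become (708 − m)/(4000 − m) and (708 + m)/(4000 + m). The pooled rate stays at 1416/8000 = 0.177.
- m = 40: 668/3960 v 748/4040, P = 0.054.
- m = 41: 667/3959 = 16.85% v 749/4041 = 18.54%. z = 0.01687 / √[0.177 × 0.823 × (1/3959 + 1/4041)] = 0.01687/0.00853 = 1.98, P = 0.048.
- m = 73: 635/3927 = 16.17% v 781/4073 = 19.18%, a difference of 3.0 points, as large as the planned effect (17.7% to 14.7%).

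Forty-one patients are 0.5% of 8000, but 41/708 = 5.8% of one group's events. The equal split is an assumption, because the groups are self-selected and poor compliers go to control.

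**The case against.** The strongest reply is that the direct contradiction is one sentence against another, and that the rest is inference.

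- **A reader might infer that grouping and matching are settled with outcomes in view.** The article does not say so. It fixes the timing, not who can see the outcome fields, and it does not say that the matching model is chosen at that point. The model's specification may stand in an analysis plan that is not shown, so its absence counts for nothing. This part of the reply stands.
- **The grouping rule is pre-set.** This also stands, and it narrows discretion considerably. The remaining latitude on duration is first of all a problem of definition. It becomes a bias problem only if it is resolved by someone who can see outcomes.
- **Researchers could form the groups and pass codes to independent statisticians.** That would satisfy {17a}, but not {16b}, and Unblinding and allocation has the researchers compare the outcomes as well.
- **{16c} does not contradict {17a} directly.** Correct: it does so only through the content of the uploaded data.
- **The 41-patient figure is contrived.** It moves only patients with recurrence, all one way. Moving 41 patients regardless of outcome leaves the expected difference at zero. It shows how sensitive the comparison is to selective reclassification and does not predict any.
- **An open-label study needs no masking.** That may be so, but this article claims a masked analysis.

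**Conclusion.** The point holds in a limited form. {16b} contradicts the last sentence of {17a}, and Unblinding and allocation fits neither cleanly. Because the group variable is created from intake after follow-up, and matching depends on it, the masked analysis claimed in {17a} is not secured by the procedures the article describes. This rests on the text and on the order of events, not on any assumption about conduct. Outcome-driven grouping or matching is a risk that the design leaves open. The documents give no evidence that it is planned or has happened, and no basis for putting a number on it. The 41- and 73-patient figures illustrate a worst case under an assumed equal split. The sample size calculation is not affected. The matter should be corrected before groups are formed. The article reports that recruitment was still under way.

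**What to change.** Reconcile {16b}, {17a} and Unblinding and allocation into one sequence:

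1. Derive the group variable by the pre-set compliance rule from a restricted extract of medication records that holds no outcome fields. The differing statements on duration in {6b}, {11a} and Unblinding and allocation must be reconciled first, so that the rule gives one answer for each patient.
2. Fit the propensity model and form the matched set from baseline data and group only, then freeze both with a date stamp.
3. Only then link the outcomes. Give the analysing statistician an A/B-coded file without butylphthalide fields, and open the codes once the primary result is final.

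Replace the sentence "At the end of the whole research cycle, biostatisticians will unblind and analyze the data" to match, and name who carries out each step. If this separation cannot be provided, withdraw the claim of a masked analysis in {17a} and report the analysis as unmasked.

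The cost is protocol wording, one extra data-lock step and a restricted extract. The extract is needed because the data management experts in Plans for assessment and collection of outcomes {18a} review all uploaded data, so giving them the grouping task with their usual access would not separate it from the outcomes. No patients or visits are added.

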### Implementation {16c}

Doctors will recruit patients with ischemic stroke who meet the inclusion criteria, and give them standardized treatment. Research assistants invite the patients into the patient management Wechat group and collect the baseline information of the patients. Biostatisticians are responsible for collecting and analyzing the uploaded data of each center. It embodies the characteristics of real world research in the process of implementation.

### Real world research settings

#### Intervention measures

In order to better reflect the efficacy of butylphthalide soft capsules in the real world, doctors will make medication plans for secondary prevention according to their condition when they are discharged, and recommend (rather than forcing) patients to take butylphthalide. The researchers will not take other interventions for the secondary prevention of patients.

#### Data collection

The research assistants will follow up the patient at 1, 3, 6, 12 months after discharge through the Internet(such as WeChat Mini Programs), and faithfully collect the patient’s condition. In addition, WeChat Mini Programs will send CRF forms to patients to obtain their medication information.

#### Unblinding and allocation

At the end of the study cycle, the researchers will reveal the actual medication information of the patients, taking patients with good butylphthalide compliance as the butylphthalide group, and patients without taking butylphthalide and patients with poor compliance as the control group, and compare the difference of outcomes between the two groups.

## Assignment of interventions: blinding

### Who will be blinded {17a}

A research assistant will be responsible for following up the participants in every research center. Researchers, research assistants and statisticians will be masked to allocate treatment throughout the treatment period. No blindness is allowed only in the event of serious adverse events (SAE) or emergency rescue. Statistical analysis will be conducted by independent statisticians who only know the group code and do not know the corresponding interventions.

### Procedure for unblinding if needed {17b}

No blindness is allowed only in the event of serious adverse events (SAE) or emergency rescue. When serious adverse reactions occur, the doctor in charge of the center who knows the the exact grouping of patients will deal with them immediately and inform research assistant to report them in time.

## Data collection and management

### Plans for assessment and collection of outcomes {18a}

The patient’s baseline information will be collected by the research assistant while in hospital. During follow-up period, the doctor regularly makes video calls with the patient, conducts detailed consultations with the patient, collects the patient’s follow-up information and fills it in the CRF form. Afterwards, all research data will be sorted by the research assistants of each center and uploaded to the EDC platform. The data management experts of the research center conduct a unified review of the uploaded data to ensure the accuracy and completeness of the data. We will remove those centers with poor data quality, missing follow-up information, and high dropout rates from continuing to participate in the study.

### Plans to promote participant retention and complete follow-up {18b}

In order to encourage the subjects to complete follow-up and improve their compliance, all subjects in each center will be assigned to the patient management Wechat group by the the doctor in charge. In Wechat group, doctors and research assistants can record the enrollment time of patients, make an appointment for follow-up, and answer questions in time. In addition, we have developed a WeChat follow-up mini program in which patients can sign in daily and write their own stroke diary.

### Data management {19}

All data will be documented on CRF that records all information at baseline and follow-up, and immediately uploaded in the database through the EDC (Electronic Data Capture) system. The CRF includes demographic data, living habits, medical history, follow-up data, and adverse events. The data will be entered into the database by a designated operator and checked repeatedly by the research center. The whole process is anonymous. In order to protect the privacy of patients, their registration number will be used instead of their real name when filling out the form. Dropouts and adverse events (adverse events) will be recorded in a timely manner. In order to ensure the high quality of the trial, members of the Quality Management Committee will train all researchers involved in the trial in accordance with standard operating procedures before the trial starts.

### Confidentiality {27}

The whole process is anonymous. In order to protect the privacy of patients, their registration number will be used instead of their real name when filling out the form. The patient’s personal information (such as home address, telephone number, Wechat account and others)will be kept strictly confidential throughout the study. All hard copy CRF will be kept by authorized researchers only. Data such as eCRF is stored in the dedicated Aliyun server of Northwest University. We will minimize the number of data processing personnel to ensure data confidentiality.

### Plans for collection, laboratory evaluation and storage of biological specimens for genetic or molecular analysis in this trial/future use {33}

Not applicable.

## Statistical methods

### Statistical methods for primary and secondary outcomes {20a}

The Kaplan–Meier method is used to draw the survival analysis curve of the percentage of patients with recurrent stroke within 1 month, 3 months, 6 months and 1 year of follow-up. The LogRank method is used to compare the statistical difference in the survival curve between the two groups. The COX proportional regression model is used to calculate the risk ratio (hazards ratios) and 95% CI.

The measurement data (such as NIHSS score and modified Rankin score) is expressed by x ± s, and t-test or Wilcoxon rank sum test is used for comparison between groups. The counting data (such as clinical efficacy and adverse reactions of the two groups) is expressed by chi-square test or Fisher exact test. The subgroup analysis is carried out according to sex, age, medical history and type of stroke.Propensity score matching (PSM) is taken to ensure that the covariates are balanced and comparable. A two-sided *P* value of 0.05 or less is considered statistically significant. All the analyses are done with SPSS software 18.0 or based on R software 3.4.3.

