## Methods: participants, interventions and outcomes

### Study setting {9}

We will recruit 8000 subjects from the following 78 hospitals. The list of recruitment hospitals can be found in supplementary material 1. All subjects in each treatment arm of the study will participate voluntarily after informed consent is obtained. Follow-up will be arranged at months 1, 3, 6, 12 after discharge. The project team leader communicates with the researchers of each center on a regular basis and conducts study visits in all research centers.

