### Exclusion criteria

Subjects will be excluded in our study if they satisfy the following criteria:Discharged, transferred to another department or died within 24 h;Severe heart, liver, kidney and other organs dysfunction or severe systemic diseases expected to survive less than one year;Can not be followed up continuously;Allergic to butylphthalide;Pregnancy, lactation or planned pregnancy;Severe mental disorders or dementia.

All patients will be recruited voluntarily and informed consent should be signed. If it is not in the patient’s interest, the patient could withdraw from the study. The reason for each withdrawal patient should be assessed and recorded in the electronic case report form (eCRF).

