### Outcomes {12}

#### Primary outcome

##### Recurrence rate of stroke

The proportion of recurrent stroke in patients with ischemic stroke.

Recurrent stroke is defined as a new neurological deficit at least 24 h after the incident stroke according to the World Health Organization definition excluding edema, mass effect, brain shift syndrome or hemorrhagic transformation, and procedure-related strokes [30].

Our researchers will follow up patients and compare the recurrence rate of stroke between the butylphthalide group and the control group at month1, 3, 6 and 12. We will ask the patient’s condition in detail in every follow-up after discharge. If the stroke relapses, the researchers will record the time of recurrence, location of the lesion, TOAST classification, occlusive vessels, sequelae, complications, other diagnoses and related examination results. The researchers will discuss with his doctor in charge to carefully identify whether the patient has a relapse or initial progression.

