##### Adverse events

Adverse events include emerging clinical cardiovascular events within one year (sudden death/ myocardial infarction/ arrhythmia/ heart failure, etc.), and other adverse reactions of patients in the trial group. During the follow-up period, we will add tests for other adverse reactions such as liver and kidney function, bleeding and blood coagulation.

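### Kaplan–Meier is named for the percentage with recurrent stroke, but death is a competing event outside the endpoint; if deaths are censored, the 12-month percentages would be somewhat too high

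*Protocol article*

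**What the plan says.** The protocol article defines the primary outcome, under the heading on recurrence rate of stroke, as a proportion: "The proportion of recurrent stroke in patients with ischemic stroke". It is compared at months 1, 3, 6 and 12, and the visit plan matches: "Follow-up will be arranged at months 1, 3, 6, 12 after discharge".

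The section on statistical methods for primary and secondary outcomes {20a} names three tools:

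- Percentages: "The Kaplan–Meier method is used to draw the survival analysis curve of the percentage of patients with recurrent stroke", at the same four time points.
- Test: "The LogRank method is used to compare the statistical difference in the survival curve between the two groups".
- Effect measure: "The COX proportional regression model is used to calculate the risk ratio (hazards ratios) and 95% CI".

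Death is not a component of the primary outcome. The only death named as an outcome is sudden death, in the adverse events section, within an open list of cardiovascular events: "sudden death/ myocardial infarction/ arrhythmia/ heart failure, etc". The article does not say how a death without recurrence enters the Kaplan–Meier curve, names no competing-risk estimator and gives no expected mortality. One exclusion criterion will hold mortality down: "Severe heart, liver, kidney and other organs dysfunction or severe systemic diseases expected to survive less than one year".

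**The concern.** The estimator and its target do not match. The target is the share of enrolled patients who have a recurrent stroke by a given month. A patient who dies first stays in the denominator and never enters the numerator. Kaplan–Meier with deaths censored treats that patient as someone who could still have a recurrence later, and so gives the risk in a hypothetical population in which nobody dies. That figure exceeds the proportion in any group in which deaths precede recurrences.

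This is more than a detail left to an analysis plan, because the article itself fixes the estimator, the quantity and the time points.

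At stake are the absolute recurrence percentages and, to a lesser degree, their difference. The excess need not be equal in the two groups. Patients choose their treatment, and the groups are formed at study end: good compliers form the butylphthalide group, and refusers and poor compliers form the control group. If compliance is counted against the full planned course, which the article does not spell out, early deaths would tend to fall in the control group and raise its curve more.

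**Working it through.** **The plan's own figure.** The sample size section assumes 17.7% and 14.7% at one year, two-sided alpha 0.05 and 90% power, and states about 3168 per group. The standard two-proportion formula gives 3168, with power 0.900. Dividing by 0.85 for 15% dropout gives 3728, against 3727 stated. The calculation rests on two plain proportions and does not involve the curve estimator.

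**Inputs for the check.** The values 17.7% (control) and 14.7% (butylphthalide) are from the sample size section and are taken here as what one minus Kaplan–Meier would read at 12 months. The one-year mortality D before any recurrence is not in the document. It is an assumption, shown from 1% to 10%.

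**Formulas (constant hazards, t in years).**

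- Recurrence hazard: λ = −ln(1 − p), which is 0.1948 for 17.7% and 0.1590 for 14.7%.
- Death hazard: μ = −ln(1 − D).
- One minus Kaplan–Meier with deaths censored: 1 − exp(−λt).
- Actual proportion with recurrence: λ/(λ+μ) × [1 − exp(−(λ+μ)t)].

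**Example.** For D = 5%, μ = 0.0513. In the control group, 0.1948/0.2461 × (1 − exp(−0.2461)) = 17.27%, so 17.7% is too high by 0.43 points.

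**Twelve months, equal mortality in both groups.**

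| D | Control, actual (excess) | Butylphthalide, actual (excess) | Difference | Risk ratio |
|---|---|---|---|---|
| 1% | 17.61% (0.09) | 14.63% (0.07) | 2.99 | 0.830 |
| 2% | 17.53% (0.17) | 14.56% (0.14) | 2.97 | 0.830 |
| 3% | 17.44% (0.26) | 14.48% (0.22) | 2.96 | 0.830 |
| 5% | 17.27% (0.43) | 14.34% (0.36) | 2.93 | 0.830 |
| 10% | 16.83% (0.87) | 13.97% (0.73) | 2.86 | 0.830 |

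Here D is a net risk, meaning the mortality that would be seen without recurrences. If D is instead the observed share who die without recurrence, μ is solved from μ/(λ+μ) × [1 − exp(−(λ+μ))] = D. The control proportion is then 17.22% at 5% and 16.74% at 10%, an excess of 0.48 and 0.96 points, and the difference is 2.92 and 2.83 points. The two definitions agree within 0.1 point on each percentage.

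**By time point (control, D = 5%).**

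| Month | One minus Kaplan–Meier | Actual | Excess |
|---|---|---|---|
| 1 | 1.610% | 1.607% | 0.003 |
| 3 | 4.753% | 4.723% | 0.03 |
| 6 | 9.28% | 9.16% | 0.12 |
| 12 | 17.70% | 17.27% | 0.43 |

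**Unequal mortality at 12 months (Kaplan–Meier difference 3.00 points).**

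- 5% control, 3% butylphthalide: 17.27% − 14.48% gives 2.78 points from unrounded values, or 2.76 with D as the observed share.
- 10% control, 5% butylphthalide: 16.83% − 14.34% = 2.49 points, or 2.43 with D as the observed share.

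**The case against.** The strongest reply is that the article does not say that deaths are censored, and that the handling of deaths normally belongs to a full protocol or analysis plan, which is not shown. That stands against any flat statement that the percentages are overstated: the point is conditional on the usual handling. It does not remove the mismatch between the named estimator and the stated proportion.

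A second reply also stands: the planned comparison does not rest on the curve. With deaths censored, the log-rank test and the Cox model compare the recurrence hazard among patients still alive and free of recurrence, which is a legitimate comparison. A reader might infer that the main test or the sample size is invalid. The documents do not support that, since the test keeps its meaning and the 3168 per group does not depend on the curve.

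A reader might also set an excess of 0.5 to 1.0 points beside the 3-point planned gap and conclude that 16% to 32% of the effect is at risk. That sets the error in one group's level against a difference between two groups. With equal mortality most of it cancels: 3.00 becomes 2.92 at 5% deaths and 2.83 at 10% on the observed-share definition, a loss of 3% (0.08/3.00) to 6% (0.17/3.00).

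Mortality may also be low. The age limit is 80, patients expected to survive less than one year are excluded, visits run from discharge, and only deaths before a recurrence compete. At 1% to 3% the 12-month excess is 0.3 points or less.

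Finally, the unequal death rates are illustrative and have no support in the documents. The self-selection and end-of-study grouping that make them possible are a larger problem, which a different curve estimator would not repair.

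**Conclusion.** The point holds in conditional form and is minor. The article assigns Kaplan–Meier to a quantity that it does not estimate once patients can die without a recurrence. If those deaths are censored, the 12-month percentages would be too high by about 0.1 to 1.0 points for assumed competing mortality of 1% to 10%. The 6-month figures would be too high by less (about 0.1 point at 5%), and the 1- and 3-month figures hardly at all.

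The between-group difference would move by about 0.1 to 0.2 points under equal mortality of 5% to 10%, with the risk ratio essentially unchanged. Under the assumed unequal rates it would move by about 0.2 points (5% and 3%) to 0.5 points (10% and 5%), in the direction that flatters butylphthalide if control deaths are the more frequent.

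All sizes rest on assumed death rates and constant hazards, because the document gives no mortality. It also cannot be said that deaths other than sudden death go unrecorded: the list in the adverse events section is open-ended, so the text is merely not explicit.

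**What to change.** In the section on statistical methods for primary and secondary outcomes:

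- Estimate the recurrence percentages at 1, 3, 6 and 12 months by the Aalen–Johansen cumulative incidence function, with death without recurrence as a competing event.
- Keep the log-rank test and Cox model, say that deaths without recurrence are censored in them, and label the Cox result a cause-specific hazard ratio.
- Record the date of every death, not only sudden death, and report deaths by group beside recurrence, so that readers can see whether mortality differs.

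The cost is small. The estimator is available in R, which the article already names, and the design, sample size and hypothesis test stay as they are. Follow-up forms may need an explicit field for death from any cause. The one downside is that the reported percentages fall slightly, which should be kept in mind when they are set beside Kaplan–Meier figures from other studies.
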